### Intervention

For the verum, 20,000 IU (Dekristol® 20,000 I.E., Mibe GmbH Arzneimittel) or 2000 IU colecalciferol (two tablets Dekristol® 1000 I.E., Mibe Arzneimittel GmbH) are encapsulated and filled up with a mixture of mannitol and colloidal silicon dioxide (Füllstoff DAC). The placebo consists solely of the hard gelatine capsules with filler. To ensure blinding, verum and placebo capsules are indistinguishable regarding appearance, quantity, weight, and packaging.

Patients, who have consented to participate in the trial, are randomly allocated to either vitamin D_3_ or placebo for a total of 12 weeks (84 days).

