#### *Compliance*

To ensure a high adherence to the trial protocol, all patients are thoroughly instructed orally at regular visits and in writing via the patient information documents. Daily intake of study medication and potential adverse events (AEs) are recorded in the patient diary. The participant can agree to receive a weekly SMS, reminding them to take their medication and fill in the diary. It will be allowed to take forgotten maintenance doses of the week on the day of the SMS reminder.

The investigator documents the supply of the trial medication as well as the return of unused loading dose capsules and/or empty packages. The coordinating center (Division of Clinical Epidemiology and Aging Research at the German Cancer Research Center, Heidelberg) keeps records of the return of unused maintenance dose capsules and/or empty packages. Intake of less than 80% of the trial medication will be defined as incompliance.

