#### *Visit 1 (start of the treatment phase, day 1)*

After checking the in- and exclusion criteria, eligible patients will be included in the clinical trial. The trial physician will hand out the trial medication to the participant for the first 28 days. This includes the entire quantity of capsules for the calculated loading dose and the amount of the daily maintenance dose that supplies the patient until visit 2 and one additional week to prevent any interruptions of the intervention. Along with the trial medication, participants will receive a patient diary in which the intake of medication and potential AEs during the upcoming treatment period of 12 weeks are recorded.

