#### *Visit 2 (day 12–21)*

At the end of the stay in the rehabilitation clinic, the participants will have completed the intake of the loading dose. To check their compliance, the patients will be asked to bring the empty trial medication packages of the loading dose and any leftover medication to this visit. A blood and urine sample will be collected to monitor biomarkers and safety parameters including hypervitaminosis D, hypercalcemia, hypercalciuria, and renal dysfunction. All suspected cases of AEs reported by the participants are assessed by the trial physician. Once it is confirmed that none of the safety parameters meet any of the criteria for discontinuation, the patient receives the remaining trial medication for the days 29 to 84. If any clinically relevant abnormalities are detected, the intake of the trial medication will be stopped immediately and further measures initiated, as appropriate.

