A priori defined subgroup analyses will be conducted for groups defined by age (< 65 / ≥ 65 years), sex (male / female), CRC stage (I or II / III), 25(OH)D levels at screening (< 30 / ≥ 30 nmol/L), season at screening (Dec-Feb/Mar-Mai/Jun-Aug/Sept-Nov), BMI at screening (< 30 / ≥ 30 kg/m^2^), FACIT-F fatigue subscale at screening (≤ 34 / > 34 points), mild to moderate anemia at screening (hemoglobin 8–10 mg/dl / > 10 mg/dl), chemotherapy and/or radiotherapy in 9 months before screening (yes / no), chemotherapy and/or radiotherapy during trial (yes / no), geriatric depression scale (GDS-15) score at follow-up (< 5 / ≥ 5 points), insomnia at follow-up (EORTC QLQ-C30 insomnia item < 3 / ≥ 3 points), pain at follow-up (EORTC QLQ-C30 pain scale < 6 / ≥ 6 points), use of strong opioids (ATC codes N02AB03, N02AA01, N02AG01, N02AA51, N02AA03, N02AG04, N02AA53, N02AA05, N02AJ18, N02AJ19, N02AA55, N02AA56, N02AJ17, N02AX06, N02AE01, and N02AA25) at follow-up (yes / no), use of psycholeptics (ATC code N05) at follow-up (yes / no), and use of corticosteroids for systemic use (ATC code H02) at follow-up (yes / no).

In addition, a subgroup analysis will be conducted for study participants, who most likely profit from the vitamin D_3_ intervention because the following conditions apply combined (yes / no): No protocol deviations (patients did not withdraw consent during the trial, were adherent to the trial medication (defined as taking at least 80% of all capsules), and did not take vitamin D_3_ or vitamin D analogs in addition to the trial medication), FACIT-F fatigue subscale ≤34 at screening, and neither use of strong opioids nor psycholeptics at follow-up.

A mean difference ≥ 3 FACIT-F fatigue subscale points will be considered a clinically relevant difference [19].

Depending on the availability of future funding for genotyping of all randomized trial participants, further subgroup analyses are planned that stratify trial participants by genetic susceptibility for low 25(OH)D levels or cancer related fatigue [38, 39].

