In the following, we describe the statistical methods of an observational sub-project for the secondary outcome “25(OH)D level”. This solely observational research project shall be addressed in those 228 VICTORIA trial participants who received the personalized vitamin D_3_ intervention and adhered to the trial medication (defined by taking at least 80% of the trial medication capsules), which will result in a final sample size *n* < 228. If 25(OH)D levels or log-transformed 25(OH)D levels are normally distributed (to be tested with a Shapiro-Wilks test), a linear regression model will be carried out with a continuous 25(OH)D level variable. In addition, a logistic regression model will be used with a dichotomized 25(OH)D level variable (< 50 nmol/L / ≥ 50 nmol/L) as the dependent variable.

Covariates for the linear and logistic regression model will be study center, age, sex, baseline 25(OH)D, compliance up to time of blood sampling, difference between exactly calculated and rounded supplied loading dose, number of days between last intake of trial medication and blood sampling, season at recruitment, baseline BMI, baseline waist circumference, baseline smoking, baseline physical activity, baseline physical functioning (EORTC QLQ-C30 subscale), baseline Charlson Comorbidity index, baseline frailty, baseline FACIT-F fatigue subscale, GDS-15 total score ≥ 5 points (at baseline), baseline anxiety (GAD-7 score), baseline pain (EORTC QLQ-C30 pain scale), CRC stage, time since CRC tumor surgery, stoma, concomitant use of vitamin D products (at follow-up), chemotherapy and/or radiotherapy in 9 months before trial (yes / no), chemotherapy and/or radiotherapy during trial (yes / no), concomitant use of laxatives (at baseline and/or follow-up), concomitant use of other drugs limiting vitamin D_3_ bioavailability at baseline and/or follow-up (phenytoin, barbiturates, systemic glucocorticoids, rifampicin, isoniazid, cholestyramine, orlistat, dactinomycin or systemic azole-antimycotics), nutritional vitamin D intake (at follow-up), appetite loss (at baseline and/or follow-up), sun exposure in last summer before baseline, skin type, solarium use in last 2 months before baseline, frequency of diarrhea (at baseline and/or follow-up), vitamin D binding protein levels and single nucleotide polymorphisms (SNPs) previously shown to be associated with low 25(OH)D levels. If appropriate, missing covariate values will be imputed with multiple imputation.

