Mean 25(OH)D levels and proportions of study participants with 25(OH)D levels < 50 nmol/L will be presented distinctly for factors that were statistically significant (*p* < 0.05) determinants of achieved 25(OH)D levels.

The analyses will be carried out both for the 25(OH)D measurement from day 12–21 (end of loading dose consumption) and for the 25(OH)D measurement from week 13–16 (end of maintenance dose consumption).

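### The exploratory 25(OH)D sub-project selects patients on whole-course adherence even for the day 12–21 level, so it drops patients for what happens after that sample and, in part, because of its result

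*Protocol article*

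**What the plan says.** All references are to the Protocol article.

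- **Selection rule.** Under Statistical methods, the sub-project is restricted to participants who received vitamin D and "adhered to the trial medication (defined by taking at least 80% of the trial medication capsules), which will result in a final sample size" below 228. No period is attached to the 80%.
- **Outcomes.** "The analyses will be carried out both for the 25(OH)D measurement from day 12–21 (end of loading dose consumption") and for the week 13–16 measurement. No separate set is defined for either time point.
- **Visit 2.** The section Visit 2 (day 12–21) has a sample taken to monitor biomarkers and "safety parameters including hypervitaminosis D, hypercalcemia, hypercalciuria, and renal dysfunction". Medication for days 29–84 is handed over only if no discontinuation criterion is met, and "If any clinically relevant abnormalities are detected, the intake of the trial medication will be stopped immediately". The section Dose modification also stops treatment at once for a diagnosed overdose.
- **The 80% rule elsewhere.** Compliance gives the general definition: "Intake of less than 80% of the trial medication will be defined as incompliance". The subgroup expected to profit most consists of patients who "were adherent to the trial medication (defined as taking at least 80% of all capsules"). The per-protocol definition also uses 80%, but spares patients whose treatment was ended for safety. The sub-project rule has no such clause.
- **A time-limited measure exists.** The sub-project's covariate list includes compliance measured up to each blood draw. It is used for adjustment, not for selection.

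**The concern.** The day 12–21 level reflects capsules taken before the sample. A whole-course adherence rule judges the patient mostly on capsules due afterwards, which has two consequences.

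1. Valid day 12–21 values are lost from patients who took the loading dose as planned and then stopped or lapsed early for any reason. This costs precision, and it can bias the results if lapsing is related to the level or to its determinants.
2. A high 25(OH)D value in that sample can itself end treatment, and ending treatment then removes the patient from the analysis of that value. This is truncation on the dependent variable. Compared with the set of patients adherent up to the sample, it lowers the mean, removes patients only from the class at or above 50 nmol/L, and tends to attenuate linear slopes.

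The sub-project asks which patients reach which level on the personalised loading dose, so the selection bears directly on its question. It is also one of the analyses planned at the interim look.

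**Working it through.** **Inputs from the article.** Treatment lasts 84 days (Intervention: "are randomly allocated to either vitamin D_3_ or placebo for a total of 12 weeks (84 days")). The loading dose is at most 420,000 IU in capsules of 20,000 IU over 11 days, followed by one 2,000 IU maintenance capsule a day. Visit 2 falls on day 12–21. "The trial physician will hand out the trial medication to the participant for the first 28 days" (Visit 1). The loading equation aims at 80 nmol/L. The vitamin D arm has 456/2 = 228 patients.

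**Reproducing the plan's figures.** 420,000/20,000 = 21 loading capsules. Days 12–84 give 73 maintenance capsules. The total dose is 420,000 + 73 × 2,000 = 566,000 IU, which matches the stated maximum. The longest course is therefore 21 + 73 = 94 capsules. With up to 11 loading capsules at one a day, the course is 84 capsules.

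**Share of the course taken by a perfectly adherent patient**

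| Last intake | 84-capsule course | 94-capsule course |
|---|---|---|
| Day 12 | 12/84 = 14.3% | 22/94 = 23.4% |
| Day 21 | 21/84 = 25.0% | 31/94 = 33.0% |
| Day 28 (first supply used up) | 28/84 = 33.3% | 38/94 = 40.4% |

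The 80% mark needs 0.80 × 84 = 67.2, so 68 capsules (day 68), or 0.80 × 94 = 75.2, so 76 capsules (day 11 + 55 = 66). No patient stopped at visit 2 can reach it. If the denominator were only the first 28-day supply, the shares would be 12/28 = 42.9% to 22/38 = 57.9% at day 12, and 21/28 = 75.0% to 31/38 = 81.6% at day 21, so most would still fail.

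**Possible size of the truncation.** The article gives neither the 25(OH)D level that triggers a stop nor a stop rate. The following are assumptions for illustration: levels are normal with mean 80 nmol/L (the equation's target) and SD 20, and the top fraction p is stopped for high 25(OH)D and removed. With a = Φ⁻¹(1 − p) and λ = φ(a)/(1 − p):

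- the mean shifts by −20λ;
- the variance ratio is δ = 1 − aλ − λ²;
- the linear slope of a determinant with explained variance R² is multiplied by δ/[1 − R²(1 − δ)];
- the share below 50 nmol/L rises from Φ(−1.5) = 6.68% to 6.68%/(1 − p).

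| p | Implied level 80 + 20a (nmol/L) | λ | Mean shift (nmol/L) | δ | Slope factor, R² 0.2 / 0.4 | Share below 50 |
|---|---|---|---|---|---|---|
| 2% | 121 | 0.049 | −1.0 | 0.896 | 0.92 / 0.93 | 6.8% (+0.1) |
| 5% | 113 | 0.109 | −2.2 | 0.810 | 0.84 / 0.88 | 7.0% (+0.4) |
| 10% | 106 | 0.195 | −3.9 | 0.712 | 0.76 / 0.80 | 7.4% (+0.7) |

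**The lower end.** With the same mean and an assumed trigger of 125 nmol/L, 1.2% (SD 20) to 3.6% (SD 25) would be removed, about 3 to 8 of 228. At 150 nmol/L it is 0.02% to 0.26%, fewer than one patient.

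**Losses unrelated to safety.** The plan assumes 10% drop-out for the primary endpoint. Applied to the arm, this is 0.10 × 228 ≈ 23 patients. Those among them who leave early after visit 2 would lose their day 12–21 value even if no safety stop ever occurred. How many that is cannot be derived from the article.

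**The case against.** The strongest reply is that this is an exploratory, purely observational sub-project, that few patients may be stopped at visit 2, and that the detail of its analysis sets belongs in an analysis plan that is not shown. The wording on all capsules comes from the subgroup definition. The sub-project refers only to the trial medication capsules and does list compliance up to each sample. All of this limits the weight of the point. It does not remove it, because the article states the selection rule outright, applies it to both time points, and nowhere limits it to capsules due by the sample.

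Several stronger readings are tempting but not supported:

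- **That overshoot is hidden.** Outcomes and endpoints makes the frequency of hypervitaminosis D, hypercalcemia, hypercalciuria and renal dysfunction at both times a secondary endpoint, and the interim analysis covers all safety parameters. None is stated to use this set. The sub-project's own cut-off is 50 nmol/L, so it looks mainly at failure to reach sufficiency.
- **That the trial's main 25(OH)D result is biased.** The one-sample test of the intervention-group mean against 50 nmol/L is not described as using this set.
- **That every coefficient shrinks.** The attenuation above applies in expectation to a linear slope under sharp truncation. It was not worked out for the logistic model, and stops for calcium, urine calcium or renal function need not lie in the upper tail of 25(OH)D.
- **That the net mean must be too low.** The 80% rule also removes ordinary non-adherers, so its total effect against the full arm is not established. Only the part due to stops for high 25(OH)D has a known direction.
- **That the per-protocol and most-likely-to-profit definitions contradict each other.** They serve different purposes, and requiring actual intake in the second is defensible.

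**Conclusion.** The point holds as a defect in the definition of one exploratory analysis set. For the day 12–21 level, the 80% rule conditions on later intake that cannot have affected the outcome. For patients stopped because of high 25(OH)D in that sample, it conditions on the outcome itself. That every fully adherent patient stopped at visit 2 is lost follows from the capsule count, given that the 80% refers to the whole course.

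The size does not follow from the article. It runs from about zero to, under the assumed normal distribution with mean 80 and SD 20 nmol/L and 2–10% stopped, a mean too low by 1.0–3.9 nmol/L, a share below 50 nmol/L too high by about 0.1–0.7 percentage points, and linear slopes reduced by roughly 7–24%. The upper end needs one vitamin D patient in ten to be stopped for a high level. Nothing here touches the primary endpoint, the test of mean 25(OH)D or the safety endpoints. It is worth correcting because the correction is cheap, not because the trial's conclusions depend on it.

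**What to change.** Define the sub-project's analysis set separately for each time point.

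- **Day 12–21:** include every vitamin D patient with a sample who took at least 80% of the capsules scheduled up to that sample, and keep those whose treatment was stopped on its result. The time-limited compliance measure already listed as a covariate supplies what is needed.
- **Week 13–16:** keep the 80% whole-course rule, and report patients stopped for safety separately, with their number, reason and last 25(OH)D value.

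The change should be in place before the interim analysis, which includes this sub-project. It needs no new data and alters no clinical rule. The cost is two analysis sets instead of one, so results at the two time points will come from slightly different patients and the report must say so.

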#### *Intervention arm*

The vitamin D_3_ treatment consists of a personalized loading dose, followed by a daily maintenance dose of 2000 IU. Several clinical trials have highlighted that 25(OH)D levels, achieved by vitamin D_3_ intake, strongly depend on a person’s 25(OH)D level and weight at baseline [29–31]. In order to provide the trial participants with a sufficient vitamin D_3_ dose, an equation to calculate individual loading doses is applied. The equation includes the baseline 25(OH)D level and body mass index (BMI) [31]:

Loading dose = 165 * BMI [kg/m^2^] * (70 – baseline 25(OH)D level [nmol/L]).

The equation by Jansen et al. was developed to increase 25(OH)D levels to 80 nmol/L, which is slightly above the generally accepted optimal level of 75 nmol/L [32]. In order to avoid non-physiological high doses of vitamin D_3_, the loading dose will be distributed in daily doses of 20,000 IU, which resembles the maximum amount of vitamin D_3_ that can be naturally produced in the skin by sunbathing in a swimsuit on a summer day [33]. The reasons for this are not safety concerns but mechanistic considerations regarding the vitamin D_3_ metabolism: Unbound vitamin D_3_ in the serum is of major importance for effective vitamin D activity [34, 35]. Its bioavailability in turn is higher when doses are given on a daily basis while avoiding single high doses [34, 35].

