### Statistical methods

All analyses will be done using SAS software version 9.4 or higher. Homogeneity of the treatment groups will be described by comparison of the demographic data and the baseline values of key variables. All statistical tests will have a two-sided significance level of 0.05. Besides, 95% confidence intervals will be estimated for all outcomes in the placebo and verum group.

The primary analysis will test the null hypothesis.

H_0_: The FACIT-F fatigue subscale at week 13–16 is the same in the two groups.

versus the alternative hypothesis.

H_1_: The FACIT-F fatigue subscale at week 13–16 is different in the two groups.

The primary endpoint FACIT-F fatigue subscale will be analyzed with an intention-to-treat approach. The intention-to-treat population will include all randomized study participants with data for the primary endpoint and who did not withdraw consent during the trial. A per-protocol analysis will be done additionally as a sensitivity analysis. The per-protocol population will exclude study participants who meet the following criteria:
Fatigue questionnaire missing at trial week 13–16Error in timing of collection of fatigue questionnaire at trial week 13–16After enrollment, it becomes evident that patient met exclusion criteria at time of recruitment or did not meet inclusion criteria.Incompliance to trial medication (defined as intake of less than 80% of capsules) unless treatment was terminated due to safety reasonsSelf-reported intake of vitamin D or vitamin D analogs in addition to the trial medication.Criteria for discontinuation of study medication were met but study medication intake was continued.

We will test on normal distribution for the outcome FACIT-F fatigue subscale with the Shapiro-Wilks test. If normal distribution can be assumed, the primary test statistic will be the two-sample t-test for the mean difference. If normal distribution cannot be assumed for the FACIT-F fatigue subscale, we will log-transform the FACIT-F fatigue subscale and test for normal distribution once more with the Shapiro-Wilks test. If normal distribution can neither be assumed for FACIT-F fatigue subscale nor log-transformed FACIT-F fatigue subscale, a Wilcoxon Rank-Sum test will be applied. In addition, appropriate 95% confidence intervals will be estimated for the FACIT-F fatigue subscale in the two groups and for the difference in FACIT-F fatigue subscale between the two groups.

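### Determinants sub-project: the linear model for achieved 25(OH)D is fitted only if the raw or log levels pass a Shapiro-Wilk test, a condition that linear regression does not need (minor)

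*Protocol article*

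**What the plan says.** The rule is in the protocol article, Statistical methods, under the exploratory sub-project on determinants of achieved 25(OH)D. The population is "those 228 VICTORIA trial participants who received the personalized vitamin D_3_ intervention and adhered to the trial medication", so fewer than 228 patients.

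Two models are planned:

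- **Linear, conditional:** "If 25(OH)D levels or log-transformed 25(OH)D levels are normally distributed (to be tested with a Shapiro-Wilks test), a linear regression model will be" fitted to continuous 25(OH)D.
- **Logistic, unconditional:** "In addition, a logistic regression model will be used with a dichotomized 25(OH)D level variable", cut at 50 nmol/L.

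Both use the same list of more than 30 covariates. Means and proportions below 50 nmol/L "will be presented distinctly for factors that were statistically significant" at p < 0.05. The analyses are done at day 12-21 and at week 13-16, and the interim analyses include the sub-project.

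The same section gives the two-group comparisons a fallback when raw and log values both fail normality (the Wilcoxon test). It names no alternative model for continuous 25(OH)D in the sub-project.

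**The concern.** The condition tests the wrong thing. Linear regression makes its distributional assumption about the errors given the covariates. At about 200 patients, inference on coefficients tolerates moderate non-normality even there. The marginal distribution of 25(OH)D mixes the error with every determinant. The listed covariates include baseline level, compliance, concomitant vitamin D products, SNPs and days since last intake. If one of these has a strong effect, the marginal distribution becomes a mixture and may fail the test although the linear model is correct. The rule can therefore remove the full-scale analysis because a determinant exists.

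The normality test also rejects more often as the sample grows, which is when regression needs normality least. Interim and final runs, or the two time points, could end up with different models for the same question. Since only significant factors are presented in detail, a normality p-value can then influence which determinants are reported.

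**Working it through.** **Inputs from the document.** Tests are two-sided at 0.05. The sub-project has n < 228 and no power calculation of its own. The trial's own sample size reproduces: 2 × 10.8² × (1.960 + 0.842)² / 3² = 203.4, so 204 per group by normal approximation; the t-test solution is 204.4, so 205; and 410 / 0.90 = 455.6, so 456. Taking 10% off 228 gives 205, used here as the upper sample size. The interim has 228 participants with week 13-16 samples, so about 114 on vitamin D at 1:1.

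**Assumed, not in the document.** The SD of achieved 25(OH)D, its shape, the share below 50 nmol/L and the strength of any determinant are not given. The mean of about 80 follows the loading-dose equation, which "was developed to increase 25(OH)D levels to 80 nmol/L". With SD 18 and normal levels, the share below 50 is Φ((50 − 80)/18) = Φ(−1.67), about 5%. The range shown is 5-50%.

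**Step 1: power once only the cut remains.** For a normal outcome cut so that a proportion p lies below, the relative efficiency is ARE = φ(z_p)² / [p(1 − p)]. For a determinant with 80% power in the linear model, power with the cut is Φ(√ARE × (1.960 + 0.842) − 1.960).

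| Share < 50 nmol/L | ARE | √ARE × 2.802 | Power | Simulated, n = 205 |
|---|---|---|---|---|
| 50% | 0.637 | 2.235 | 61% | 61% |
| 30% | 0.576 | 2.126 | 57% | 58% |
| 20% | 0.490 | 1.961 | 50% | 54% |
| 10% | 0.342 | 1.639 | 37% | 42% |
| 5% | 0.224 | 1.326 | 26% | 29% |

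The simulation (600 runs per row, no other covariates) gave 79-81% for the linear model. When about 40 parameters were assumed, the logistic fit failed in 18% of runs at 10% below 50 and in 89% at 5%. The linear model kept about 80%.

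**Step 2: how often raw and log levels both fail.** The table gives simulated rates of Shapiro-Wilk rejecting both at 0.05, with mean about 80 and SD about 18 unless the CV is given. Repeat runs differ by a point or two.

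| Shape of the levels | n = 180-205 | n = 114 (interim) |
|---|---|---|
| Normal or log-normal | 3-4% | 3-4% |
| Gamma, CV 0.25-0.35 | 7-39% | 3-11% |
| 10% low responders, 25-40 nmol/L lower | 11-62% | 9-41% |
| t with 10 df | 29-34% | 20% |
| t with 5 df | 76-81% | 55% |

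**Step 3: can a determinant close the gate by itself?** Here the residuals are exactly normal, n = 205, with one binary determinant:

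- 15% of patients at −25 nmol/L (residual SD 18): both tests fail in about 13%.
- 20% at +40 nmol/L (residual SD 15): about 37-41%.
- 40% at +35 nmol/L (residual SD 14): about 73%.

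In each case the linear model including that determinant is exactly right.

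**Step 4: combine.** The loss in Step 1 is 80 − 61 = 19 to 80 − 26 = 54 points and applies only when both tests fail. Multiplying by a 4% failure rate gives about 1-2 points on average. Multiplying by 80% gives about 15-43 points.

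**The case against.** Several objections carry weight.

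- **Importance.** The sub-project is labelled exploratory and observational, and uses vitamin D recipients only. The between-arm 25(OH)D comparisons and the one-sample test against 50 nmol/L are separate analyses, and the interim run has no consequence for the trial. This stands and sets the severity.
- **Frequency.** A reader might infer that the linear model will often be lost. The document does not support that: log levels get a second chance, and it gives no SD and no evidence of heavy tails or a low-responder group. Some features point the other way: patients taking under 80% of capsules are excluded, other vitamin D is prohibited, and the loading dose is adapted to baseline level and BMI. The upper rates need either t-like tails or a group about 2 SD lower.
- **The missing branch.** The article does not say that the continuous analysis is dropped if both tests fail; it names nothing else. The full protocol or analysis plan may do so. That limits certainty about the consequence, but the condition itself is stated here and is unnecessary.
- **The logistic model.** It is not a fallback. It runs regardless, at the threshold the trial uses for its own success criterion, so there is no ground for demoting it.

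What remains is that the condition tests a property that linear regression does not need and can block a valid model.

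**Conclusion.** The point holds as a minor one. The condition on the linear model is unnecessary and can be triggered by the effects being sought. If raw and log levels both fail, a determinant with 80% power in the linear model keeps about 61% at best (half of patients below 50 nmol/L) and 26-37% if 5-10% are below. The chance of that cannot be settled from the document; under the assumed mean and SD it runs from about 3-4% to about 80% depending on shape. The power figures assume a normal outcome and one determinant without loss to other covariates.

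A stronger reading would be that the plan loses its continuous analysis in most realistic cases, or that the trial's conclusions are at risk. Neither is supported: the failure rate is an assumption, and nothing in the sub-project feeds the primary endpoint.

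**What to change.** In the sub-project text of Statistical methods:

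1. Delete the normality condition and always fit the linear model to continuous 25(OH)D.
2. Fix the scale (raw or log) in advance.
3. Check residuals rather than the marginal distribution.
4. If residuals show heteroscedasticity, use a named small-sample robust variance (for example HC3) or a bootstrap.
5. Keep the 50 nmol/L logistic model as the planned additional analysis.

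The cost is a sentence or two of wording and no new data. Robust errors are not free with many covariates, so the variant should be named. In simulations with 40 parameters and constant error variance, HC3 widened standard errors by 12-15% at n = 180-205 and 25-27% at n = 114. The unadjusted HC0 gave 7-10% type I error at n = 180-205 and 12-14% at n = 114.

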#### *Interim analyses*

No interim analyses are planned for the primary outcome FACIT-F fatigue subscale in trial week 13–16 and the following ones have no implications for the ongoing of the trial.

Interim analyses are planned with the first half of the intended final sample size to be randomized, i.e. 228 study participants with available blood samples from week 13–16. The analyses will be focused on 25(OH)D-related secondary outcomes, all safety parameters and for the exploratory sub-project: “Determinants of the achieved 25(OH)D levels by the personalized vitamin D_3_ intervention”.

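### The determinants sub-project fits about 39 parameters in a plain logistic model with about 0.8 to 2.6 events per parameter, and again at interim with fewer; the linear model does not share this fault

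*Protocol article*

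**What the plan says.** The protocol article, under Statistical methods, describes an exploratory and purely observational sub-project on what determines the 25(OH)D level reached on vitamin D. It is confined to adherent patients in the vitamin D arm, "which will result in a final sample size *n* < 228".

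Two models share one covariate list. A linear regression is fitted if 25(OH)D or its logarithm passes a Shapiro-Wilk test. In addition, "a logistic regression model will be used with a dichotomized 25(OH)D level variable (< 50 nmol/L / ≥ 50 nmol/L) as the dependent variable". The list opens with "Covariates for the linear and logistic regression model will be study center, age, sex, baseline 25(OH)D, compliance up to time of blood sampling" and closes with "vitamin D binding protein levels and single nucleotide polymorphisms (SNPs) previously shown to be associated with low 25(OH)D levels".

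Results are then shown by factor: they "will be presented distinctly for factors that were statistically significant (*p* < 0.05) determinants of achieved 25(OH)D levels". The text does not say which of the two models supplies those factors. Both sampling times, day 12-21 and week 13-16, are analysed.

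The section on interim analyses plans a look at 228 participants with week 13-16 blood samples: "The analyses will be focused on 25(OH)D-related secondary outcomes, all safety parameters and for the exploratory sub-project". It adds that the interim analyses have no bearing on the continuation of the trial.

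**The concern.** In logistic regression the information comes from the smaller outcome group, not from the number of patients. The loading-dose equation is described as developed to reach 80 nmol/L, so patients below 50 nmol/L should be a minority. With 35 covariates in the model, the number of such patients may be close to the number of parameters.

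Ordinary maximum likelihood then overstates odds ratios, its Wald tests reject too often, and with sparse binary covariates it can separate or fail to converge. A rule that highlights every factor with p < 0.05 would pass those errors on as determinants. At stake is how far the sub-project's list of determinants can be trusted, most of all at interim.

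**Working it through.** **1. The plan's own sample size.** For a difference of 3 points, SD 10.8, two-sided 0.05 and 205 per group, the two-sample t-test has power 0.801, so 205 is reproduced. Then 410 / 0.90 = 455.6, rounded up to 456, and 456 / 2 = 228 per arm, the ceiling for the sub-project. No size or power is stated for the sub-project itself. Applying only the 10% drop-out gives 228 × 0.90 ≈ 205; this is an assumption, and non-adherence would lower it further.

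**2. Parameters.** The list has 35 items: 34 others, and SNPs as the 35th.

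- Three clinics need 2 parameters (+1) and four seasons need 3 (+2): 34 + 3 = 37 before SNPs.
- Stage in three classes instead of two adds 1: 38.
- With the SNPs the total is about 39 or more. I use 39.

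**3. Events per parameter** = n × share below 50 nmol/L / 39. The share is not in the documents; 15-50% is assumed, and 50% is the most favourable value possible.

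| n | 15% | 25% | 50% |
|---|---|---|---|
| 205 (final) | 30.8 / 39 = 0.8 | 51.3 / 39 = 1.3 | 102.5 / 39 = 2.6 |
| 114 (interim) | 17.1 / 39 = 0.4 | 28.5 / 39 = 0.7 | 57 / 39 = 1.5 |

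The interim figure is 228 / 2 = 114 by 1:1 allocation. It is an upper limit, because non-adherent patients are still to be removed.

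**4. Simulation of the logistic model.** There are 39 independent covariates, one with a true log-odds of 0.40 and 38 null. The nominal count of false positives is 38 × 0.05 = 1.9.

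| n = 205 | 15% | 25% | 50% |
|---|---|---|---|
| Maximum likelihood, estimate of 0.40 | 0.61 | 0.54 | 0.52 |
| Null terms with p < 0.05 | 3.3 | 3.1 | 3.0 |

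A Firth-type penalised likelihood at n = 205 gives estimates of 0.38-0.41 and 1.2-1.9 false positives over the same range.

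At n = 114, maximum likelihood separates or fails to converge in 71% of data sets at 15% events and 16% at 25%, and rarely at 50%. Where it converges, the estimate is roughly doubled; even at 50% events it is about 0.71.

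**5. Sensitivity.** A second simulation was harsher: three true effects (odds ratio 1.6 per SD) and some binary covariates at 5% prevalence.

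- At n = 205, failure was 71 / 24 / 8 / 4% at event shares of 10 / 20 / 30 / 50%.
- At n = 114, failure was 100 / 81 / 44 / 24% at the same shares.
- At n = 205, 2.9-3.7 of 36 null terms reached p < 0.05 (nominal 1.8), and true effects were inflated 1.3-1.6 fold.

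Failure rates therefore depend heavily on the assumptions. The inflation and the excess of false positives at n = 205 appear at every event share tried.

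**6. Linear model.** With the same 39 terms it gave about 1.9 of 38 null terms at p < 0.05, which is nominal. Nominal is still not zero: if all 35 listed factors were null, 35 × 0.05 = 1.75 false determinants are expected per fit, and the chance of at least one is 1 − 0.95^35 = 83% under independence. The plan makes such fits at two time points.

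**The case against.** The strongest reply is that this is an exploratory, observational sub-project in which the linear model comes first and the logistic model is an addition. Significance is used only to choose the factors for which means and proportions are tabulated. The interim look changes nothing in the trial. The share below 50 nmol/L is unknown, the simulated covariates are invented, and the absence of penalisation is inferred from plain wording; estimation detail may stand in a document not shown.

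Much of this stands. A reader might infer that all determinants from the sub-project will be unstable. The documents do not support that, because the linear model keeps its error rate under its assumptions. A reader might also infer that false determinants would steer dosing; nothing in the article gives the results that use. Nor should drop-out be taken off the interim 114 again, since the interim is already defined by available week 13-16 samples.

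Three things remain. The model, the covariate list, the p < 0.05 rule and the interim repeat are all fixed in the article, so this is a choice made and not a detail left open. The bias and the excess false positives persist even at the most favourable event share. And the linear model is conditional on a Shapiro-Wilk test of the outcome: if both scales fail, the logistic model is the only one the text names.

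**Conclusion.** The concern holds for the logistic model. At about 205 patients and 15-50% below 50 nmol/L, there are about 0.8-2.6 events per parameter, a true log-odds of 0.40 is estimated at about 0.5-0.6, and about 3 of 38 null terms reach p < 0.05 where 1.9 are expected. At 114 patients the estimate roughly doubles. The fit fails in about 70% of data sets at 15% events and 16% at 25%, and rarely at 50% under the main assumptions (24% under the harsher ones).

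This rests on an assumed event share, 39 independent covariates and ordinary maximum likelihood. Correlated pairs on the list, such as BMI and waist circumference, would add instability.

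The linear model is sound in its error rate, with about 1.75 false determinants per fit if all 35 factors are null. The primary analysis and the conduct of the trial are unaffected. Severity is low to moderate.

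**What to change.** - Say that the factors highlighted at p < 0.05 come from the linear model. Check its assumption on residuals and not on the outcome's own distribution, so that a failed Shapiro-Wilk test does not leave the logistic model alone.
- Fit the logistic model by Firth-type penalised likelihood, or with a reduced covariate set named in advance.
- Do not fit the full-list maximum-likelihood logistic model at interim.
- Report the highlighted factors as hypothesis-generating.

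The cost is analysis-plan wording, slightly more programming and a less detailed interim determinant analysis. Data collection, sample size and treatment do not change. Which reduced set to use, or whether to screen the remaining covariates by another method, is a matter of preference.
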